### Outcome variables

The primary outcome measure of this study will be recovery rate. ‘Recovered’ will be defined as when a child attains a MUAC ≥12.5 cm and WHZ scores ≥ − 2, without bipedal edema. The secondary outcomes are the mean recovery time and average weight gain. Children who developed SAM during the study and/or persisted as moderately malnourished at the end of the 3-month follow-up will be considered to have failed the management for MAM.

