**Methods:**

A randomized controlled non-inferiority trial will be conducted with moderately wasted children aged 6 to 59 months in Wolaita, Ethiopia. The calculated sample size is 324 (i.e. with 162 children in each of two arms, to be assigned by randomization). The daily ration will be: 100 g of LIBS plus 25.2 g of sugar with 8 ml oil in the intervention group, and 150 g of CSB+ with 16 ml of oil in the control group. These interventions will be provided for a maximum period of 12 weeks, with follow-up performed on a weekly basis. Data analysis will be done using SPSS and STATA software. Both intention-to-treat and per protocol analyses will be done. Hazard ratio and Kaplan-Meier (log rank) curves of survival analysis will be done to predict the probability of recovery rate. Logistic regression will be used to test for interactions between independent and dependent variables. Analysis of variances, t-tests, fisher’s exact test and chi-square tests will be used to assess baseline characteristics.

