In a study done in South-Western Ethiopia, without having a targeted nutrition-specific supplement to address MAM, only half of children aged 6 to 59 months recovered from MAM within 28 weeks of follow-up, with health and dietary counseling services alone. They were provided such services according to the national policy, but the recovery rate remained unsatisfactory. Even though these districts are named as food-secure areas, there are food-insecure households with acute moderately malnourished children suffering from high rates of deterioration and no improvement with the existing management. This is because household food insecurity is not determined by the food security level of districts [2].

Clinical strategies on the management of SAM have been present for many years. The implementation of these strategies has yielded positive outcomes. However, consistent study on the management of MAM is lagging behind, and much of the data is published on SAM, even if MAM is more prevalent and a gateway to developing SAM [8–10].

Children with MAM living in food-insecure areas are getting corn soya blend plus (CSB+) as a conventional supplement. Generally, CSB+ is given as a treatment to MAM children in developing countries since it has a good nutritional value for limited cost. However, there has been considerable argument in the international nutrition community concerning the nutritional suitability and competence for the treatment of MAM. CSB+ is believed by some to be a poor choice as a treatment since it does not contain important nutrients in acceptable amounts; it contains comparatively high amounts of anti-nutrient and fiber. In addition, it has a generally low fat level, and thus needs vegetable oil in order to provide the essential fatty acids and energy [11]. According to the report of different literature, the recovery rate after 8 to 16 weeks follow-up with CSB+ treatment is within the range of 67 to 76.8% [12–14].

The nutritional management of MAM have to normally be initiated on optimum usage of Local ingredient-based nutritious food [4]. Local ingredients based supplementary food are available, accessible, can be formulated at the household level and contain adequate amounts of the required nutrients [13].

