### Sample size calculation

The proportion of children who recover from MAM in an area where there is a supplementary feeding program (CSB+) is about 67% [12]. The sample size assumes that the expected percentage response in an experimental group is 60% and in a control group is 67%, with the non-inferiority criterion set to be an absolute value of 7%. To achieve 80% power to demonstrate non-inferiority, it is estimated that 162 subjects per group would be required, including a 10% withdrawal rate. This leads to a total required sample size of 324 subjects. The anticipated 10% dropout rate was used based on the observed dropout rate reported in two studies [12, 13]. For this sample size calculation, the PharmaSchool sample size calculator for non-inferiority trials was used.

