### Data analysis

All data collection sheets will be controlled by the field supervisors for completeness. EpiData version 3.1 will be used for all data entry. Two data clerks will enter data simultaneously to ensure data quality. Continuous data quality evaluation will be made through automatic consistency checks. Statistical significance is set at 5% for all analyses. Statistical analysis will be done using SPSS and STATA software for survival and hazard ratio. The probability of recovery rate will be predicted in Kaplan-Meier (log rank) curves of survival analysis. T-tests, analysis of variance (ANOVAs) and chi-square tests will be used to assess baseline characteristics. In accordance with recommendations for analyzing and reporting equivalence and non-inferiority trials, both intention-to-treat (ITT) and per protocol (PP) analyses will be done, and the 95% CI will be used to infer whichever variances are significant [24]. The ITT analyses will include all children enrolled in the study whereas the PP analyses will exclude children who lost to follow-up, refused and transferred out of the management programme but include children discharged as cured, died or non-cured.

Logistic regression will be used to test for interactions between the recovery rate and other variables. Mean recovery time and median recovery time, mean differences of MUAC and mean difference between WHZ scores will be computed to describe the magnitude of the difference between the two groups.

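### Mean recovery time is a named secondary outcome not tied to the survival analysis, although the planning rates leave 33% to 40% of children with no recovery time at week 12

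*Protocol article*

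**What the plan says.** Under Outcome variables, the protocol article makes recovery rate the primary outcome and adds: "The secondary outcomes are the mean recovery time and average weight gain". Children who develop SAM, or who are still moderately malnourished when follow-up ends at three months, are classed as treatment failures. They are given no recovery time.

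Under Data analysis: "Mean recovery time and median recovery time, mean differences of MUAC and mean difference between WHZ scores will be computed". The stated purpose is to describe how far the two groups differ. The same section plans Kaplan-Meier curves with a log-rank test, a hazard ratio, and both intention-to-treat and per-protocol analyses. The Kaplan-Meier curves are tied to the probability of recovery. The mean recovery time stands in a later paragraph, beside the mean differences in MUAC and WHZ.

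On the time limit, the Abstract (Methods) says: "These interventions will be provided for a maximum period of 12 weeks, with follow-up performed on a weekly basis". Participant timeline agrees: follow-up visits finish within 11 weeks and end-line data come one week later.

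On how many children will recover, Sample size calculation assumes that the "expected percentage response in an experimental group is 60% and in a control group is 67" per cent.

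**The concern.** A mean time to recovery needs a time for every child. Here the design itself stops the clock at 12 weeks, and the planning figures say that a large minority of children will still be unrecovered. For them the time is known only to exceed 12 weeks, so an unrestricted mean cannot be estimated without extrapolating.

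Two workable readings remain. One is the mean restricted to 12 weeks over all children, which is the area under the Kaplan-Meier curve and keeps the randomised comparison. The other is the average among children who recovered. That average compares two subsets selected by the primary outcome. A food that fails slow responders removes those children from its own average, which shortens its apparent recovery time. The text does not choose between the two readings, and they can give different answers, even in direction.

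At stake is a secondary statement that children recover about as fast, or faster, on LIBS, in a trial that asks whether LIBS is as effective as CSB+.

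**Working it through.** **Inputs**

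- Time limit T = 12 weeks (Abstract, Methods; Participant timeline, 11 + 1 weeks).
- Recovery p = 0.67 on CSB+ and 0.60 on LIBS; 162 children per arm (Sample size calculation). I read these rates as 12-week proportions, which is the horizon in the Hypothesis section. The sample size section attaches no time to them.
- For CSB+, Background reports that "the recovery rate after 8 to 16 weeks follow-up with CSB+ treatment is within the range of 67 to 76.8" per cent.
- The plan gives no figure for recovery time, so there is none to reproduce. The timing patterns below are my assumptions.

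**Step 1. Children without a recovery time**

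- CSB+: 1 − 0.67 = 33%, and 0.33 × 162 ≈ 53 children.
- LIBS: 1 − 0.60 = 40%, and 0.40 × 162 ≈ 65 children.
- At the top of the reported CSB+ range: 1 − 0.768 ≈ 23%.

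Both planned rates exceed 50%, so the median over all children can still be estimated.

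**Step 2. Constant recovery rate, 67% vs 60%**

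Formulas: rate λ = −ln(1 − p)/12; mean among recoverers = 1/λ − 12(1 − p)/p; restricted mean over all children = p/λ.

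- CSB+: λ = 1.1087/12 = 0.0924. Recoverers: 10.82 − 5.91 = 4.91 weeks. Restricted mean: 0.67/0.0924 = 7.25 weeks.
- LIBS: λ = 0.9163/12 = 0.0764. Recoverers: 13.10 − 8.00 = 5.10 weeks. Restricted mean: 0.60/0.0764 = 7.86 weeks.

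The difference is 0.18 week among recoverers and 0.61 week on the restricted mean. The recoverers-only figure hides 1 − 0.18/0.61, about 70% of it. The direction does not reverse.

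**Step 3. Same 67% vs 60%, lost recoveries are late ones**

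Assume 40% of each arm recover at week 4, and a further 27% (CSB+) or 20% (LIBS) at week 10.

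- CSB+: recoverers (0.40×4 + 0.27×10)/0.67 = 6.42 weeks; restricted mean 1.6 + 2.7 + 0.33×12 = 8.26 weeks.
- LIBS: recoverers (0.40×4 + 0.20×10)/0.60 = 6.00 weeks; restricted mean 1.6 + 2.0 + 0.40×12 = 8.40 weeks.

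Among recoverers, LIBS looks 0.42 week faster. Over all children it is 0.14 week slower.

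In a simulation of this pattern (146 per arm; early times uniform over weeks 2 to 6, late times over weeks 8 to 12), the food with fewer recoveries had the shorter recoverers-only mean in about 83% of trials, significantly so in about 15%.

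**Step 4. LIBS works in only part of the children**

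Assume 62% of LIBS children respond, at 0.20 per week, and CSB+ is as in Step 2. This departs from the planned 60%.

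- LIBS recovery by week 12: 0.62 × (1 − e^−2.4) = 56.4%.
- Recoverers: 1/0.20 − 12 e^−2.4/(1 − e^−2.4) = 5 − 1.20 = 3.80 weeks, against 4.91 on CSB+.
- Restricted mean: 0.38×12 + 0.62×(1 − e^−2.4)/0.20 = 4.56 + 2.82 = 7.38 weeks, against 7.25 on CSB+.
- Median over all children: solving 0.38 + 0.62 e^(−0.2t) = 0.5 gives 8.2 weeks, against ln 2/0.0924 = 7.5 weeks on CSB+.

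Among recoverers, LIBS looks 1.1 weeks faster. The restricted mean shows no advantage (0.13 week slower), and the median also shows LIBS slower.

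**The case against.** The strongest reply is that no sentence limits the mean to recovered children. A reader might infer that the outcome exists only for recoverers, and the documents do not support that. The planned survival analysis could supply a 12-week restricted mean with no change to the data, and the intention-to-treat commitment to include every enrolled child points that way. This stands, so the point is an unsuitable and unlinked summary, not a declared recoverers-only analysis.

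It can also be said that censoring rules belong in an analysis plan, which is not shown. That is right for the detailed rules. But the article itself fixes the plain mean as the outcome and as a description of the difference between arms. That choice does not fit a design in which 33% to 40% are expected to be unrecovered.

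Other safeguards are real. The median over all children, the log-rank test and the hazard ratio do not depend on selecting recoverers. In Step 4 the median and the recovery rate both count against LIBS, so the mean would not be the reader's only evidence.

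A reader might also infer that the mean will generally favour the worse food, or will always be pulled toward no difference. Neither follows. Step 2 shows shrinkage without reversal. Steps 3 and 4 show reversal only under timing patterns that the protocol does not state, and in Step 4 the recoverers-only gap (1.1 weeks) is larger than the restricted-mean gap (0.13 week).

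Finally, recovery requires both MUAC and WHZ, while Data collection takes MUAC weekly but weight and height monthly. Differences of a fraction of a week may be finer than this schedule can resolve, so the figures illustrate direction and relative size.

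**Conclusion.** The concern holds as a point about one secondary outcome. On the planning rates, 33% of CSB+ and 40% of LIBS children have no recovery time by week 12, and the named mean is not tied to the analysis that could handle them. If it is computed among recoverers, it compares subsets chosen by the primary outcome. With constant recovery rates, the difference falls from 0.6 to 0.2 week. With some assumed timing patterns, the sign changes.

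The 33% and 40% rest on the protocol's own rates read as 12-week proportions. The sizes in weeks rest on my assumed timing patterns and on continuous observation.

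The tempting larger conclusion, that the non-inferiority claim itself is at risk, is not supported. The hypothesis and the primary outcome rest on recovery rate, which this point does not touch. The change is worth making because it is cheap and removes the possibility of a misleading statement about faster recovery.

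**What to change.** In Outcome variables and Data analysis, replace mean recovery time with: restricted mean time to recovery over 12 weeks in all randomised children, estimated as the area under the Kaplan-Meier curve to week 12.

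State the handling of children without recovery:

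- Children who remain malnourished, develop SAM or die are counted as not recovered through week 12.
- Children lost to follow-up are censored at their last assessment. They should not be scored as 12 weeks: a 10% withdrawal rate is anticipated, and scoring them that way treats unknown outcomes as failures and can dilute a difference in a non-inferiority trial.

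Report the between-arm difference with its 95% CI. Keep the median, read from the same curve. Label any mean among recovered children as descriptive only.

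The cost is a change of wording in two sections and a small addition to the survival analysis already planned. It needs no new visits, measurements or children. The downside is that the restricted mean is less directly comparable with published recoverers-only means, which can still be shown descriptively.

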### Participant timeline

Children aged 6 to 59 months will be assessed for MAM based on inclusion and exclusion criteria using MUAC and weight-for-height/length z-scores. The screening procedure will end within 3 weeks. Consenting of the eligible respondents (mothers of children aged 6 to 59 months) and randomization of the eligible subjects will take place 1 week after screening completed during which the subjects will be allocated into intervention and control groups, along with baseline data collection. Follow-up interviews with the anthropometric assessment will be done weekly and monthly basis after the allocation date and completed within 11 weeks. End-line data collection will take place 1 week after ending a follow-up interview (Fig. 2).

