### Study population

The study population will be children with MAM, MUAC of ≥11.5 cm and < 12.5 cm without bilateral edema and/or with weight-for-height z-scores between − 3 to − 2 Standard Deviations [4, 5]. Mothers or caregivers of selected children will be the respondents.

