### Inclusion criteria

All children 6 to 59 months of age identified as MAM (MUAC of ≥11.5 cm and < 12.5 cm) [5].

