### Recruitment of study participants and randomization

Data collectors with health extension workers will visit all households with children aged 6 to 59 months. They will assess for eligibility by measuring the children’s MUAC. If the child has a MUAC of < 12.5, data collectors will register and send the caregiver with the child to the actual screening site, where MUAC will be re-measured and weight and height or length will be taken. Children aged 24 to 59 months will be measured for weight and height, and children aged 6 to 23 months will be measured for weight and length. In addition to the values of MUAC (i.e. 11.5 cm to 12.5 cm), we will use the z-scores of weight for height or weight for length for recruitment (i.e. weight-for-height z-scores: between − 3 to − 2 Standard Deviations). If the child is identified as moderately malnourished according to the MUAC and not according to the values of weight-for- height/length z-scores, we will recruit them with their MUAC values. The screening procedure will be conducted by trained data collectors and facilitated by health extension workers using both MUAC and WHZ. Edematous malnutrition will also be evaluated using bilateral pitting edema criterion. The screening process will be continued until the sample size is met.

Computer generated sequentially numbered randomization list that contained codes for children who meet enrolment criteria will be prepared by the research supervisor. These children will be randomized into intervention or control groups, using random allocation software. The allocation ratio will be 1:1 (Fig. 1).

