### Data collection

Selected caregivers of children with MAM aged 6 to 59 months will be interviewed for collection of baseline data such as socio-demographic and economic status, dietary habits, child’s age, breastfeeding practices and history of child and maternal illness. The child’s weight will be noted using a seca weight scale to the nearest 0.1 kg. The data collectors will be sure that the scale is placed on a flat, hard, even surface and will weigh with minimal clothing.

Height will be recorded to the nearest 0.1 cm using a seca height scale for children aged 24 to 59 months. For children aged 6 to 23 months, length will be measured to the nearest 0.1 cm using a locally made wooden measuring board. Before starting height measurement, the data collectors will ensure that the height board is on level ground and the child is without shoes; the collector will kneel in order to get to the level of the child and will encourage the caregiver to help. For length, data collectors will measure the child lying down, being sure that the length board is placed on a flat and stable surface.

MUAC will be documented by non-stretchable standard United Nations Children’s Fund (UNICEF) plastic tape measures. The measurement will be taken half-way between the acromion and the olecranon processes, with the measuring tape fitting comfortably, but without making a depression in the upper arm. Weekly assessment of anthropometric measurement using MUAC will be done by the data collectors for intervention as well as control groups. On a monthly basis, data collectors will again collect anthropometrics using the MUAC, height or length board and weight scale which are identical equipment to that used at baseline. At the same time, they will observe for bilateral pitting edema. Based on the follow-up measurement of anthropometry children who developed sever acute malnutrition will be referred to SAM clinic.

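### Eligibility readings are about 1 to 4 weeks old at randomisation and no stated rule applies the criteria to the baseline reading; separately, the study population is defined in two conflicting ways

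*Protocol article*

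**What the plan says.** **Timing.** Under Participant timeline, "The screening procedure will end within 3 weeks", and "randomization of the eligible subjects will take place 1 week after screening completed". In that same step "the subjects will be allocated into intervention and control groups, along with baseline data collection". The Fig. 2 legend describes the children randomised as those already assessed and classed as moderately malnourished.

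**Measurements.** Under Recruitment of study participants and randomization, children found at home with a low MUAC go to a screening site "where MUAC will be re-measured and weight and height or length will be taken". That repeat belongs to screening. Baseline anthropometry is implied by Data collection, where the monthly visits use the "height or length board and weight scale which are identical equipment to that used at baseline", and by the Discussion, which compares baseline with end-line MUAC and WHZ.

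**Outcome and analysis sets.** Recovery needs MUAC ≥12.5 cm, WHZ ≥ −2 and no oedema (Outcome variables). ITT keeps every enrolled child. PP drops only losses to follow-up, refusals and transfers out (Data analysis).

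**Population.** Study population defines MAM by MUAC "and/or with weight-for-height z-scores between" −3 and −2. Inclusion criteria reads "All children 6 to 59 months of age identified as MAM" and gives only the MUAC band. At the household visit a MUAC below 12.5 is the trigger on which "data collectors will register and send the caregiver with the child to the actual screening site".

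**The concern.** Children enter because a reading fell below 12.5 cm, and rising above the same value is half of the primary outcome. Measurement error and 1 to 4 weeks of natural change will carry some children across the line before any supplement is given. Recruitment also takes in children who qualify on MUAC but not on WHZ. Such a child may already satisfy the WHZ half of recovery, so that MUAC drift alone would complete the definition on day 0.

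A child who is recovered from day 0 in either arm says nothing about the relative effect of the two foods. Such children pull the observed difference toward zero, which in a non-inferiority trial makes the desired conclusion easier to reach. Neither analysis set, as described, removes them.

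The population wording is a different matter. It bears on which children the result applies to, not on drift between screening and day 0.

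**Working it through.** **1. Age of the eligibility reading.** Shortest: a child screened on the last day waits 1 week. Longest: 3 + 1 = 4 weeks.

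**2. Inputs for the dilution.** From Sample size calculation: 67% recovery on CSB+, 60% on LIBS, margin 7 points, 162 per group including 10% withdrawal. Evaluable per arm: 162 × 0.90 = 145.8, taken as 146. The 95% CI comes from Data analysis and corresponds to one-sided 2.5%. The assumed rates differ by exactly the margin, so they serve as the boundary case in which non-inferiority should be declared 2.5% of the time. (How 162 was reached is a separate question; it is used here only as the planned number.) The plan gives no figure for the share recovered at day 0, so there is none to reproduce.

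**3. Formula.** If a share f counts as recovered in both arms from day 0, the observed proportion is f + (1 − f)p and the observed deficit is (1 − f) × 7 points. With SE = √[(p_C(1 − p_C) + p_L(1 − p_L))/146], the false non-inferiority rate is Φ((0.07 − deficit)/SE − 1.96).

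| f (assumed) | CSB+ | LIBS | Deficit (points) | SE | False non-inferiority |
|---|---|---|---|---|---|
| 0 | 0.670 | 0.600 | 7.0 | 0.0562 | 2.5% |
| 5% | 0.6865 | 0.620 | 6.65 | 0.0556 | 2.9% |
| 10% | 0.703 | 0.640 | 6.3 | 0.0548 | 3.3% |
| 20% | 0.736 | 0.680 | 5.6 | 0.0531 | 4.5% |

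For f = 10%: (0.070 − 0.063)/0.0548 = 0.128, and Φ(0.128 − 1.96) is about 3.3%.

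**4. How large f might be.** All inputs here are assumptions: population MUAC normal with mean 13.8 to 14.2 cm and SD 1.1 to 1.2 cm, measurement error SD 0.15 to 0.30 cm, true gain before day 0 of 0 to 0.1 cm. Children are selected when two readings fall below 12.5 cm and the second is at least 11.5 cm. In simulation the share whose true MUAC is at or above 12.5 cm on day 0 runs from about 4% (small error, no gain) to just over 19% (mean 14.2, SD 1.1, error 0.30, gain 0.1). These are upper bounds for f, because WHZ ≥ −2 is needed too. If a third reading is taken and only children still in the band are kept, the corresponding shares fall to about 2% and 9%.

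**5. Population definition, side by side.**

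| Section | Criterion |
|---|---|
| Study population | MUAC and/or WHZ |
| Inclusion criteria | MUAC only |
| Recruitment, household visit | only MUAC < 12.5 is sent on |
| Recruitment, screening site | both measured; MUAC decides if WHZ does not qualify |

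A child who qualifies on WHZ alone belongs to the first definition but is not sent to the screening site, so the stated route cannot enrol that child.

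**The case against.** The strongest reply is that this is an article condensed from a fuller protocol. MUAC is measured twice during screening, baseline measurements accompany allocation, and the Fig. 2 legend places them before the first ration. Whether a child out of range at baseline would still be randomised may be settled elsewhere. That stands against one tempting reading, namely that nothing is checked again. The documents do not support it: a baseline reading is implied. What does stand is that the article fixes the order of steps and attaches no eligibility rule to that reading.

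Three further inferences go too far:

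- **That every child reading ≥12.5 cm at baseline is already recovered.** On the same assumptions 8% to 25% would give such a reading, but part of that is noise in a single measurement, and recovery also requires WHZ ≥ −2. Some of these children may also fall back, and the Discussion speaks of baseline and end-line measurements.
- **That a child with SAM at day 0 breaches the exclusion criteria.** Eligibility is judged at screening, so later deterioration is not strictly a breach. Under Outcome variables, SAM developing during the study counts as failure.
- **That the two population definitions cause the drift.** They do not. Recruitment also says that MUAC decides when WHZ does not qualify, which agrees with Inclusion criteria. The conflict lies mainly with the Study population wording.

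It is also fair to say that the effect is modest, and that misclassification from measurement error would exist even with same-day randomisation. Both points stand and limit the size of the concern, but neither removes it.

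**Conclusion.** Both points hold, separately.

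**Timing.** A gap of about 1 to 4 weeks follows directly from the text, and no stated rule applies the entry criteria at baseline. The direction of the resulting bias favours non-inferiority. Its size cannot be read from the documents. For f of 10% to 20% a true 7-point deficit would appear as 6.3 to 5.6 points, and the false non-inferiority rate would be about 3.3% to 4.5% instead of 2.5%. This rests on three assumptions: the MUAC distribution and error in the working, day-0 recovered children staying recovered in both arms, and the 7-point deficit applying to the remaining children. That such children will enter is likely, but the article does not state it.

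**Population.** The contradiction is plain on the page and needs no calculation. As recruitment is described, the trial can speak only for MUAC-defined MAM.

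**What to change.** 1. Take the already planned baseline MUAC, WHZ and oedema reading before allocation. Randomise only children who then still meet the trial's own inclusion and exclusion criteria, and use that reading as the baseline value. This reduces the dilution but does not remove it. If allocation has already taken place, report the share outside the criteria on the baseline reading and repeat the primary analysis in the children who met them.

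2. Reconcile Study population, Inclusion criteria and Recruitment to one definition. If recruitment stays MUAC-based, word the aim and conclusion as MUAC-defined MAM.

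**Cost.** No new measurement is needed, but more than 324 children must be listed at screening. If 8% to 25% read at or above 12.5 cm, as assumed above, that means 324/0.92 ≈ 353 to 324/0.75 = 432, plus replacements for any who read below 11.5 cm. Batch allocation and the grouping by neighbourhood must wait until the re-check is complete. The second change is one of wording only, provided recruitment stays as described.
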